### Sample size and power calculations

Based on recruitment outcomes of previous trials conducted by the research team in clinical settings and maternity services specifically, it is expected that 70% of invited women, or 15 women (average of 5 per service), will consent to participate in weekly surveys for each of the three time periods (‘first appointment’, ‘27–28 weeks gestation’, or ‘35–36 weeks gestation) (total *N* = 45 per week) [70]. This will yield 5600 data points over the course of the data collection period, sufficient to detect (with 80% power and with a Bonferroni adjusted alpha of 0.0167) for the primary outcomes a (1) 15% absolute increase in receipt of recommended assessment of gestational weight gain (baseline prevalence estimate of 40%), (2) 14% absolute increase in recommended advice (baseline prevalence estimate of 30%), and (3) 9% absolute increase in the offer of recommended referral (baseline prevalence estimate of 10%).

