### Study design and setting

A stepped-wedge controlled trial will be conducted in maternity services in three health sectors within the Hunter New England Local Health District, New South Wales, Australia. As shown in Fig. 1, measurement of the outcomes will occur continuously via telephone surveys with weekly random samples of pregnant women who have attended the maternity services in the last 2–3 weeks, from 6 months prior to the delivery of the intervention in the first sector to 12 months after intervention completion in the last sector. Delivery of the 4-month implementation intervention in the three sectors will occur sequentially. The sequential delivery will provide pre- and post-intervention outcome data periods of variable lengths for each sector, with a minimum of 12 months post-intervention data to enable the assessment of the sustainability of the intervention effect. Intervention effect will be determined by comparing the prevalence of recommended care between the pre-intervention and post-intervention periods for the three sectors combined.

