### Statistical analysis

Pre- and post-intervention primary outcome data will be analysed using mixed effects logistic regression models to detect a change in the reported receipt of each of the three elements of the best practice care pathway for addressing gestational weight gain (assessment, advice, and referral) for all three sectors combined. Separate models will be fitted for each outcome. The main predictor of interest will be a before/after intervention indicator variable as well as a fixed effect for time, and a random intercept for an antenatal time point (first appointment, ‘27–28 weeks gestation’, or ‘35–36 weeks gestation’). The implementation intervention will be declared effective if the coefficient for the intervention period variable is below the threshold of *α* = 0.0167 for any of the three primary outcomes. A time-series analysis will be performed over the post-intervention periods to determine if slope changes occur, as an indicator of sustainability. Pre- and post-intervention secondary outcome data will be analysed using mixed effects logistic regression models to detect a change in each outcome for all three sectors combined. Descriptive statistics will be used to report on the process measures. The cost analysis and practice change cost-effectiveness results will be incorporated into an economic model to project the expected costs and outcomes that would be associated with broader scale-up of the implementation intervention to antenatal services across the state. SAS (V9.3 or later) will be used for all statistical analyses.

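### The three detectable rises match one effective sample size only if the post-intervention variance is ignored; under one common design effect, referral at 9 points has less power than stated

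*Protocol article*

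**What the plan says.** In the protocol article, Sample size and power calculations, the total is introduced with "This will yield 5600 data points over the course of the data collection period". The operating characteristics are given once for all primary outcomes: "with 80% power and with a Bonferroni adjusted alpha of 0.0167". Three detectable differences follow:

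- assessment: "15% absolute increase in receipt of recommended assessment of gestational weight gain (baseline prevalence estimate of 40" per cent);
- advice: "14% absolute increase in recommended advice (baseline prevalence estimate of 30" per cent);
- referral: "9% absolute increase in the offer of recommended referral (baseline prevalence estimate of 10" per cent).

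The planned rates are therefore 40% to 55%, 30% to 44% and 10% to 19%.

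Statistical analysis says: "Pre- and post-intervention primary outcome data will be analysed using mixed effects logistic regression models to detect a change". A separate model is fitted to each outcome, with a before/after indicator, a fixed effect for time and a random intercept for antenatal time point. Success on any one of the three outcomes at 0.0167 is enough to declare the intervention effective.

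**The concern.** With one design, one N, one alpha and one power, three detectable differences should lead back to the same amount of information unless the design effect differs by outcome. These do so only if the variance of the post-intervention proportion is set equal to the baseline variance. That step is almost harmless for assessment, where the variance moves from 0.240 to 0.2475. It is not harmless for referral, where a rise from 10% to 19% takes the variance from 0.090 to 0.1539, an increase of 71%.

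Referral is one of the three outcomes that can establish effectiveness. If its power at 9 points is nearer two in three than four in five, a null referral result is weaker evidence of no effect than readers of the stated 80% would think.

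**Working it through.** **Inputs.** Alpha 0.0167 (taken as two-sided; not stated), power 80%, and the three baselines and rises, all from Sample size and power calculations. Normal quantiles: 2.393 + 0.842 = 3.235, squared 10.465. Equal pre and post numbers are assumed first. Below, n is the effective number per period after any allowance for the design, p0 and p1 are the pre and post rates, and d = p1 − p0.

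**1. Reproducing the printed figures: baseline variance in both periods.** n = 2 × 10.465 × p0(1−p0)/d².

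- Assessment: 2 × 10.465 × 0.24/0.0225 = 223
- Advice: 2 × 10.465 × 0.21/0.0196 = 224
- Referral: 2 × 10.465 × 0.09/0.0081 = 233

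Letting each d vary by half a point for rounding gives 209–239, 209–241 and 209–261, which overlap fully. Put another way, a rise of 0.303 baseline standard deviations gives 14.8, 13.9 and 9.1 points, which round to the printed 15, 14 and 9.

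**2. Using the variance of each period.** n = 10.465 × [p0(1−p0) + p1(1−p1)]/d².

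- Assessment: 10.465 × (0.2400 + 0.2475)/0.0225 = 227 (rounding range 212–243)
- Advice: 10.465 × (0.2100 + 0.2464)/0.0196 = 244 (227–262)
- Referral: 10.465 × (0.0900 + 0.1539)/0.0081 = 315 (286–349)

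Referral needs 315/227 = 1.39 times the assessment size, and the two ranges do not overlap. Other formulas agree: pooled 231/248/319, arcsine 230/247/313, log-odds 234/251/330 (referral-to-assessment ratios 1.36–1.41).

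**3. Unequal periods.** Measurement runs "from 6 months prior to the delivery of the intervention in the first sector to 12 months after intervention completion in the last sector", and "Delivery of the 4-month implementation intervention in the three sectors will occur sequentially". Assuming back-to-back steps (Fig. 1 is not shown), the total is 6 + 12 + 12 = 30 months. Sector-months before delivery are 6 + 10 + 14 = 30, and after it 20 + 16 + 12 = 48, a ratio of 1.6. With both variances the pre-period n is 184, 194 and 241 (241/184 = 1.31). The rounding ranges for assessment (172–197) and referral (218–267) still do not overlap. With baseline variance only they do: 170–194, 170–196 and 170–212.

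**4. Referral power if the design effect is common.** Power = Φ(d/√{[p0(1−p0) + p1(1−p1)]/n} − 2.393). At n = 227, where assessment has 80%, referral gives 0.09/√(0.2439/227) = 2.746, and 2.746 − 2.393 = 0.353, so power is 64%. Advice has 77%. The referral rise detectable with 80% power is 10.8 points, and about 10.5–11 points for n from 223 to 239. Over the 1:1 and 1.6:1 splits and the different formulas, referral power is about 60–72%; the upper end comes from calibrating on the advice figure instead of assessment.

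**5. Link to 5600.** Treated as independent and split 2800/2800, the data would give above 99.9% power for all three outcomes. The stated 80% therefore contains a large unprinted design allowance: 2800/227 = 12.3 for assessment and 2800/315 = 8.9 for referral.

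**6. Stepped-wedge check.** Assumed layout: three equal sectors, 30 months, delivery months excluded (5600 × 78/90 = 4,853 points), a separate effect for each month and a random sector effect. With an assumed ICC of 0.001, baseline variance gives detectable rises of 15.0, 14.0 and 9.2 points. With both variances, power at the printed rises is 79.5%, 76.2% and 63.8%. With 5600 analysed points and ICC 0.005–0.5, referral power is 66–68%.

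This agreement is sensitive to the setting. With 4,853 points and ICC 0.05–0.5, baseline variance gives 15.5–15.6, 14.5–14.6 and 9.5 points. With 5600 points and ICC 0.005–0.5 it gives 14.3–14.5, 13.4–13.6 and 8.8–8.9. Neither set reproduces all three printed figures.

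**The case against.** A reader might infer that referral power is simply about 65% and the stated 80% is wrong, or that the figures can only have come from a baseline-variance formula. The document supports neither, for three reasons.

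- **Outcome-specific design effects.** The section does not say that one ICC served all outcomes. With a design effect of 1 + (m − 1) × ICC and an illustrative m of 195, ICCs of 0.057, 0.053 and 0.040 give 80% for all three with correct variances. This stands as a possibility. That formula is for parallel clusters, however. In the stepped-wedge layout above with monthly effects, even a referral ICC of zero gives only 69% (4,853 points) or 76% (5600 points).
- **Coding of time.** The analysis section promises only a fixed effect for time. In the same layout, quarterly effects give referral power of about 74–88%, and a linear term 94–99%. This stands in full against any flat figure for referral power. It does not remove the mismatch: under a common design effect, referral was below assessment and advice in every setting run.
- **A condensed article.** Leaving the formula and ICC to a fuller document is normal and is not the point here. The point is that the figures the article does print do not agree with one another under one common design effect.

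**Conclusion.** The point holds in conditional form. The printed rises of 15, 14 and 9 points are mutually consistent with baseline variance in both periods. With the post-intervention variance and one common design effect they are not, at either a 1:1 or a 1.6:1 split. If that common effect is calibrated so that assessment has 80% at 15 points, referral at 9 points has about 60–72%, its detectable rise is about 10.5–11 points, and advice is a few percentage points short of 80%.

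This rests on a common design effect, a two-sided 0.0167 and an inferred formula. The mismatch is firm under the common design effect; the absolute power is not, because it depends on the ICC, the split and the time coding. Nor does the point show that the trial is too small: with a linear time term, referral power would exceed 90%.

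**What to change.** Rerun the power calculation for the model in Statistical analysis, using p0(1−p0) before and p1(1−p1) after, with the ICC or design effect for each outcome, the pre/post split and the time coding actually used. State those inputs beside the result. Then restate the referral entry, and advice if needed, as either the rise detectable with 80% power or the power at the printed rise.

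Replacement figures should come from that rerun. About 11 points at 80%, or 9 points at about 65%, would be right only if a single design effect calibrated to the assessment figure was used. If outcome-specific ICCs were used, printing them may be all that is needed.

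The cost is one recalculation and a corrected sentence, with a possibly less favourable stated figure for referral. Enrolment does not change.

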### Statistical analysis

Pre- and post-intervention primary outcome data will be analysed using mixed effects logistic regression models to detect a change in the reported receipt of each of the three elements of the best practice care pathway for addressing gestational weight gain (assessment, advice, and referral) for all three sectors combined. Separate models will be fitted for each outcome. The main predictor of interest will be a before/after intervention indicator variable as well as a fixed effect for time, and a random intercept for an antenatal time point (first appointment, ‘27–28 weeks gestation’, or ‘35–36 weeks gestation’). The implementation intervention will be declared effective if the coefficient for the intervention period variable is below the threshold of *α* = 0.0167 for any of the three primary outcomes. A time-series analysis will be performed over the post-intervention periods to determine if slope changes occur, as an indicator of sustainability. Pre- and post-intervention secondary outcome data will be analysed using mixed effects logistic regression models to detect a change in each outcome for all three sectors combined. Descriptive statistics will be used to report on the process measures. The cost analysis and practice change cost-effectiveness results will be incorporated into an economic model to project the expected costs and outcomes that would be associated with broader scale-up of the implementation intervention to antenatal services across the state. SAS (V9.3 or later) will be used for all statistical analyses.

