## Background

Gestational weight gain (GWG) below or above-recommended levels is a leading risk factor for poor pregnancy outcomes, with the potential for harm to both mother and child [1]. For the mother, these include a higher risk of gestational diabetes [2], caesarean birth [1], greater postpartum weight retention, and greater risk of obesity long term [3–5]. For the baby, excess gestational weight gain is associated with a higher risk of macrosomia and neonatal morbidity [6].

To quantify an ideal gestational weight gain range, in 2009, the United States Institute of Medicine (IOM) developed total and trimester-specific incremental weight gain recommendations for optimal healthy weight gain during pregnancy based on a woman’s pre-pregnancy body max index (BMI) [7]. Guidelines in Australia [8] and other high-income countries [7, 9] recommend that antenatal care providers support women to gain weight within these recommendations. Internationally, most (60–80%) women gain weight outside of these recommended target ranges [1]. In Australia, 64% of pregnant women report gaining weight outside of recommendations [10], including 85% of pregnant Aboriginal Australian women [11]. A systematic review and meta-analyses of studies including over 1.3 million pregnancies found that of the women who gained weight outside of the IOM recommended ranges, 9.5–29% gained below and 37–73% above the recommended ranges [1, 12, 13].

Cochrane systematic review evidence shows that educational and behavioural interventions supported by weight monitoring are effective in reducing the risk of unhealthy gestational weight gain by 20% (average RR 0.80, 95% CI 0.73 to 0.87) [14]. Systematic review evidence also suggests that such interventions are most effective when delivered as part of routine antenatal care [15], and it has been reported that women prefer such care to be provided in a way that is person-centred and non-judgemental [16].

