**Fig. 1 Fig1:**

Data collection and intervention timeline for the stepped-wedge trial design

The stepped-wedge study design provides pragmatic and scientific advantages relevant to the conduct of complex implementation interventions in health services [32, 45]. First, such a design provides the same level of evidence as a standard parallel cluster controlled trial [46]. Second, the design addresses the practical difficulty of recruiting enough equivalent maternity services that would be required for a parallel cluster RCT and increases study efficiency by using each group as its own control [32, 45]. Third, the design provides an opportunity for all participating services to receive the intervention, providing motivation for clinician engagement. Finally, such a design demonstrates the feasibility of the intervention in an operational environment, a key determinant of the intervention being translated into routine practice elsewhere should it prove successful [45].

In Australia, public maternity services are a key setting for the provision of antenatal care to address gestational weight gain as they provide care for 55% of all birthing women, including care for a diverse range of population groups, including those with a high prevalence of risk and those who are disadvantaged [47, 48]. The maternity services involved in this trial provide care to approximately 7000 women annually across urban and rural areas, accounting for almost 70% of women birthing in public hospitals within the health district [46].

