#### Process measures

The acceptability, adoption, fidelity, and penetration/reach of the best practice care pathway for addressing gestational weight gain and the implementation strategies from the perspective of clients and clinicians will be measured. These process measures will be based on an implementation evaluation framework specified by Proctor et al. [65] and use validated measures where available [66]. Measures to assess the penetration/reach of the implementation intervention will include the participation of antenatal clinical staff in educational meetings, interaction of clinical staff with local opinion leaders, involvement in academic detailing/audit and feedback sessions, and receipt of clinical practice guidelines. To determine penetration/reach by different groups of clinicians, data will be collected from clinicians on position/profession, level of training, and length of time working in antenatal care. Contextual factors, including measures of the social, political, or economic environment that might influence implementation (e.g. changes due to COVID-19 restrictions), will also be recorded [67].

To assess the delivery of the care pathways to different demographic groups of women, the following information will be collected: age, gender, highest level of education, employment status, geographical location, Aboriginal or Torres Strait Islander status of woman and baby, household composition, current gestation, and gestation at the first antenatal appointment, whether attending care for their first or subsequent pregnancy and pre-pregnancy BMI.

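### The stated primary model has no maternal or sector term, so case-mix differences between the women sampled before and after can enter the effect estimate, although the relevant characteristics are already collected

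*Protocol article*

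**What the plan says.** The protocol article (Statistical analysis) names the primary model's terms. The fixed part is: "The main predictor of interest will be a before/after intervention indicator variable as well as a fixed effect for time". The random part is "a random intercept for an antenatal time point (first appointment, ‘27–28 weeks gestation’, or ‘35–36 weeks gestation" and nothing more. The same section sets the alpha of 0.0167 and allows the intervention to be declared effective on any one of the three outcomes, so this is a stated confirmatory model.

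For the secondary outcomes only the model family is given: "Pre- and post-intervention secondary outcome data will be analysed using mixed effects logistic regression models to detect a change in each outcome". No terms are listed.

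Under Process measures the survey collects "age, gender, highest level of education, employment status, geographical location, Aboriginal or Torres Strait Islander status of woman and baby", together with household composition, gestation, first or subsequent pregnancy, and pre-pregnancy BMI. The stated purpose is "To assess the delivery of the care pathways to different demographic groups of women". Adjustment is not mentioned.

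Under Study design and setting, the effect is the pre/post contrast with the three sectors combined, and the pre and post periods differ in length by sector. The services "provide care to approximately 7000 women annually across urban and rural areas".

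**The concern.** The contrast compares weekly samples of women drawn before and after the intervention. Individual women are not randomised, and three sectors are too few to balance case mix by their order. Two routes can then carry case mix into the effect estimate.

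- **Between sectors.** Sectors enter the pre and post periods in different proportions, and the model has no sector term. Usual care is expected to vary by service (Usual care), and the services span urban and rural areas.
- **Within sectors.** Who is sampled or responds could change when the intervention starts. Clinicians know when their service is in the intervention period (Participant blinding). They may judge a woman inappropriate to contact, and women may opt out during the appointment (Participant eligibility and recruitment).

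Case mix plausibly bears on these outcomes. Pre-pregnancy BMI sets the weight-gain target, and gain off target adds a dietetics offer to the referral outcome where such a service exists. The Background puts off-target gain at 64% of pregnant women in Australia, "including 85% of pregnant Aboriginal Australian women".

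**Working it through.** **Timeline.** Inputs: data collection starts 6 months before the first sector's intervention and ends 12 months after the last sector's; delivery is 4 months per sector, in sequence. Then 6 + 3 × 4 + 12 = 30 months, which reproduces the stated 30-month period and fits back-to-back delivery. Fig. 1 is not shown, so that remains an assumption. So do equal sampling per sector-month and exclusion of the 4 intervention months.

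| Sector | Pre months | Post months | Share of pre (of 30) | Share of post (of 48) |
|---|---|---|---|---|
| 1 | 6 | 20 | 20% | 42% |
| 2 | 10 | 16 | 33% | 33% |
| 3 | 14 | 12 | 47% | 25% |

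The article gives no figure for case mix, so all covariate inputs below are assumptions. Logistic models were fitted to expected values on this layout with no true effect. The antenatal time-point intercept was left out. Points are log-OR × p(1−p), with p the stated baseline of 40%, 30% or 10%, so p(1−p) = 0.24, 0.21 or 0.09.

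**Route 1: stable sector differences.** Take a maternal characteristic present in 45/30/15% of women in sectors 1/2/3, with odds ratio 2 to 3 for the outcome. The low end is linear time with odds ratio 2; the high end is categorical month with odds ratio 3.

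- Assessment: 0.144 × 0.24 = 3.5 points, to 0.333 × 0.24 = 8.0
- Advice: 0.148 × 0.21 = 3.1, to 0.346 × 0.21 = 7.3
- Referral: 0.154 × 0.09 = 1.4, to 0.370 × 0.09 = 3.3

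Adding either the covariate or a sector term returns zero. The time effect enlarges this bias: without it, assessment shows only 1.1 to 1.7 points. With categorical month, the sole months holding both pre and post data are months 11 to 14, when sector 1 is post, sector 2 is in delivery and sector 3 is pre. The effect then rests on sector 1 against sector 3.

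A second check sets sector baselines at +0.2/0/−0.2 on the logit scale. The stated model gives 0.2 − (−0.2) = 0.400 with categorical month, or 0.273 with linear time. A maternal covariate unrelated to sector leaves both unchanged; a sector term gives 0.000.

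**Route 2: a shift within sectors at the intervention.** Take a characteristic that becomes 5 points more common post-intervention in every sector. By hand, bias ≈ 0.05 × risk difference. For a 50% characteristic at odds ratios 2 and 3:

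- Assessment: 0.05 × 0.165 = 0.8 and 0.05 × 0.256 = 1.3 points
- Advice: 0.05 × 0.143 = 0.7 and 0.05 × 0.222 = 1.1
- Referral: 0.05 × 0.061 = 0.3 and 0.05 × 0.092 = 0.5

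Model fits for a 30% characteristic agree: log-OR 0.035/0.055 for assessment gives 0.8/1.3 points, 0.0358/0.0569 for advice gives 0.75/1.2, and 0.0372/0.0598 for referral gives 0.3/0.5. Across both, the ranges are 0.8–1.3, 0.7–1.2 and 0.3–0.5. A sector term leaves these values unchanged; the covariate brings them to zero.

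**Drift common to all sectors.** Bias 0.000: the time effect absorbs it.

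**Precision.** For assessment with a true log-OR of 0.606 and balanced case mix, adding the covariate moves the standard error from 0.182 to 0.182 (odds ratio 1.5), 0.181 to 0.184 (2) and 0.181 to 0.187 (3). The z value goes from 3.31 to 3.32, 3.26 to 3.30 and 3.14 to 3.24, a gain of at most about 3%.

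**The case against.** The strongest reply is that this is a condensed article, that covariate lists usually sit in an analysis plan that is not shown, and that nothing rules out adjusted analyses. For the secondary models this stands. A reader might infer that they omit covariates, but the article lists no terms for them, and the two weight-gain outcomes are already given by BMI category. For the primary model it stands only in part: fixed and random terms, alpha and success rule are all stated, so one can ask whether the stated model suits the design.

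Second, the imbalance that the design builds in is one of sector, and maternal covariates remove only what they explain of it. This stands, which is why the fix must include a sector effect.

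Third, once sector is handled, what remains is small and rests on a shift that the documents do not show. Sampling is weekly and random from the same services, with one recruitment procedure throughout. A 70% consent rate or a text-message route that applies in both periods does not by itself move the contrast. This limits the size. It does not rule out a shift, because random selection acts only on women left after clinician exclusion and before opt-out and non-response.

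Fourth, the care pathway itself calculates pre-pregnancy BMI from measured height, so the completeness of reported BMI could change with the intervention. This stands and is taken up in the fix.

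**Conclusion.** The point holds as a bias concern for the three primary models. Stable sector differences pass into the estimate and a sector term removes them. A within-sector shift that coincides with the intervention is removed only by maternal covariates, and only as far as the measured ones capture it. At the assumed 5 points and odds ratio 2 to 3, that second part is about 3 to 9% of the target effects (from 0.3/9 to 1.3/15). The 3.5–8.0, 3.1–7.3 and 1.4–3.3 points from the sector route show how exposed the stated model is. They are not the gain from maternal covariates over a model with sector.

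Two stronger readings are not supported. A reader might infer that leaving covariates out costs precision, but for these binary outcomes under logistic regression the standard error does not fall when they are added. A reader might also infer that before and after samples are wholly different women whose case mix must differ. The eligibility rule bars reselection only for the same time point within 4 weeks, so women can recur, and a difference is possible rather than shown.

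The covariate prevalences, sector gaps, shifts and odds ratios are all assumptions, as are back-to-back delivery and equal sector volumes.

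**What to change.** In the Statistical analysis section, add to each of the three primary models prespecified fixed effects for age, parity, education, Aboriginal or Torres Strait Islander status and pre-pregnancy BMI category, alongside a sector effect. Keep the model without maternal covariates, but with sector, as a sensitivity analysis. State the terms of the secondary models and use the same set there. Fixing the list in advance also prevents a choice of covariates after the data are seen, which matters when one outcome of three suffices for success.

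The cost is wording, since the data are already collected. It needs a rule for missing covariates and a check, by sector and period, that BMI completeness does not change with the intervention. Adjusted and unadjusted odds ratios differ somewhat even without confounding, so a small gap between the two analyses should not be read as bias.

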### Intervention

#### Best practice care pathway for addressing gestational weight gain

A best practice care pathway for addressing gestational weight gain in pregnancy will be implemented in maternity services across the three participating sectors. The gestational weight gain care pathway is consistent with international [9] and Australian national [8] and state [49] antenatal clinical practice guidelines and is based on models of assessment and brief intervention that have been shown to support weight gain within recommended ranges [14, 15]. As shown in Fig. 2, the gestational weight gain care pathway will consist of three key care elements—assessment, advice, and referral—delivered during antenatal appointments throughout pregnancy via face-to-face, telephone, and/or video conference consultations.

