#### Implementation intervention

The following evidence-based organisational and individual clinician focused strategies will be used to support clinicians deliver the gestational weight gain care pathway as part of routine antenatal care. The specific content of each strategy and the prioritisation of resources allocated to the strategies will be tailored to the needs and context of each individual sector.

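### The primary model has one before/after coefficient and no sector term, so if the tailored effects differ by sector its "combined" result rests mainly on the first sector

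*Protocol article*

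**What the plan says.** Statistical analysis specifies a separate mixed logistic model for each primary outcome: "The main predictor of interest will be a before/after intervention indicator variable as well as a fixed effect for time", together with "a random intercept for an antenatal time point". No sector or service term is named, and neither is an intervention-by-sector term. Effectiveness is declared from this single coefficient at 0.0167.

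Study design and setting defines the target in the same pooled way: "Intervention effect will be determined by comparing the prevalence of recommended care between the pre-intervention and post-intervention periods for the three sectors combined". It also sets the timetable: "Delivery of the 4-month implementation intervention in the three sectors will occur sequentially".

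The section Implementation intervention says of the strategies: "The specific content of each strategy and the prioritisation of resources allocated to the strategies will be tailored to the needs and context" of each sector. The section on prioritising strategies describes how this is done, through barrier surveys and consultation in each sector. What all sectors share is the care pathway ("A best practice care pathway for addressing gestational weight gain in pregnancy will be implemented in maternity services across the three participating sectors") and the list of strategy types.

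**The concern.** The implementation intervention is what the trial tests, and by design its content and resourcing differ between sectors. Equal effects in the three sectors are therefore an assumption, not something the design secures. When effects differ, a single coefficient in a staggered layout is a weighted mean of the sector effects. The weights come from the timetable and the other model terms, not from the number of women served.

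The coefficient decides whether the intervention is called effective. The cost-effectiveness analysis uses cost per unit change in the primary outcome, and those results feed the projection to antenatal services across the state. If the coefficient reflects one sector's tailored version, that version is what is projected.

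**Working it through.** **Inputs from the protocol.** There are three sectors and a 4-month delivery in each, one after another. Measurement runs from 6 months before the first delivery to 12 months after the last. This gives 6 + 3×4 + 12 = 30 months, which matches the 30-month data collection period stated for pregnant women. The protocol gives no sector weights, so there is no figure of its own to reproduce on this point.

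**Assumptions.** Steps follow without gaps, so delivery starts after months 6, 10 and 14. Sectors are sampled equally, and the three antenatal time points are balanced in each sector-month. Implementation months are left out, because the section analyses pre- and post-intervention data. The calculation is a linear approximation.

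**Layout.** Pre/post months are 6/20 in sector 1, 10/16 in sector 2 and 14/12 in sector 3, which makes 78 sector-months.

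**Formula.** Regress the before/after indicator x on all other model terms and keep the residual r. The weight of sector s is the sum of r·x over its cells divided by the sum of r·x over all cells.

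**Printed terms, month effects for time.** This can be checked by hand, because a month contributes only if it holds both pre and post data:
- Months 1-10: all pre.
- Months 11-14: sector 1 post, sector 3 pre, sector 2 in delivery.
- Months 15-30: all post.

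Only months 11-14 inform the coefficient. It equals sector 1 after delivery minus sector 3 before delivery, so the weights are 100/0/0. It would also absorb any baseline difference between those two sectors.

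**All variants (sectors 1/2/3, %).**

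| Time term | Printed terms | Sector intercepts added |
|---|---|---|
| Month | 100/0/0 | 30/10/60 |
| Quarter | 87.5/12.5/0 | 26/22/52 |
| Linear | 74/28/-2 | 27/36/38 |

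Counting implementation months as post, with month time, gives 75/25/0 as printed and 19/31/50 with sector intercepts. A random instead of a fixed sector intercept gives 35/9/56 at an intracluster correlation of 0.01 and about 31/10/60 at 0.1. Sector sizes of up to 3:1 leave the printed month-time weights at 100/0/0.

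**Illustrative effects, printed month-time model.**
- 5, 5, 20 points: 1×5 + 0×5 + 0×20 = 5. The equal-weight mean is 30/3 = 10.
- 20, 15, 5 points: 1×20 + 0×15 + 0×5 = 20. The mean is 40/3 = 13.3.

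The gaps are 5 and 6.7 points. The detectable increases in the sample size section are 15, 14 and 9 points.

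**Logistic check on expected counts.** A log-odds effect of 0.9 in one sector only (mean 0.30) gives, under the printed month-time model, 0.90, 0.00 and 0.00 when that sector is 1, 2 or 3. An effect of 0.6 in every sector returns 0.6 in every model tried.

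**Precision of the equal-weight mean of three sector effects (month time).** All three effects are estimable: the design has full rank, 35 columns. In units of the residual variance per sector-month, the variances are 0.623 for the mean, 0.600 for the pooled coefficient with sector intercepts and 0.500 for the printed model. The interval ratios are √(0.623/0.600) = 1.019 and √(0.623/0.500) = 1.116. With quarters the ratios are 1.011 and 1.108; with linear time they are 1.003 and 1.102.

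**The case against.** A single common-effect coefficient is a usual stepped-wedge analysis, and if the effects are equal the weighting does no harm. The pathway and strategy list are shared, and nothing in the protocol says how far effects would differ; the effect sets above are illustrations. The form of time is left open, as a condensed article may do, and a fuller analysis plan may settle it. Outcomes by sector are also planned in the cost-consequence analysis. All of this stands, and it limits the point to the case of unequal effects. It does not remove the point. The section does state its predictor, time term, random effect and decision rule, and under every form of time tried those terms give sector 3 essentially no weight. The cost-consequence split does not supply sector estimates from the primary model.

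Three stronger readings are tempting but not supported:
- **The result would mainly describe the last sector.** The 30/10/60 weights need sector intercepts, which the section does not name. As printed, the first sector dominates.
- **Weights of 0/29/71 apply.** These arise only with sector effects, month effects and a separate common term for the implementation months. The protocol has no such term.
- **The protocol misreports an equally weighted average.** It speaks only of the three sectors combined and never says how they are weighted.

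**Conclusion.** The point holds for the model as printed. With unequal sector effects, the coefficient offered as the three-sector result is essentially a first-sector result: 100/0/0 with month time, 74/28/-2 with linear time. Sector intercepts alone do not settle it. The dominant sector then becomes the third under month or quarter time, and the weights come near to equal only under linear time. The sizes rest on the assumptions listed in the working. The direction for the printed terms did not change when implementation months were counted as post or when sector sizes were varied. How far the reported effect would miss depends on how much the sectors differ, which the protocol does not say.

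**What to change.** In Statistical analysis, add sector intercepts and replace the single before/after indicator with one before/after term per sector. Name one prespecified average of the three as the primary effect, for example the equal-weight mean, and test it at 0.0167 for each outcome. Report the three sector effects beside it. State the form of time and the handling of implementation months in the same place.

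The change is a few lines of text and one contrast per model. With implementation months left out, the interval is about 0.3-2% wider than that of a pooled coefficient with sector intercepts. It is about 10-12% wider than that of the printed model, whose extra precision comes from ignoring sector differences.
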